### Participant incentives

We will cover transportation costs incurred by adolescents and adults participating in the process evaluation and community advisory groups. They will also be offered refreshments (juice and biscuits). No incentives will be offered to adolescents participating in the baseline or endline survey, or coaching sessions.

### Post-trial care

Where required, a psychosocial counsellor employed by TPO Nepal will remain in the study setting to provide follow-up care for study participants.

### Ethics and research governance

The trial has ethical approval from King’s College London (RESCM-22/23–27,152; HR/DP-22/23–33,427) and the Nepal Health Research Council (NHRC) Ethics Committees (Ref no. 3088).

The NHRC requires caregiver consent and adolescent assent for adolescents under the age of 18, which we will adhere to in this study. We will collect consent for participation in the baseline survey and again for the endline survey. A trained researcher will explain the study to the adolescent and caregiver and give them a consent/assent form and information sheet (in Nepali). The researcher will ask the adolescent and caregiver if they have any questions about the study and make sure they are satisfied before asking them both to sign the consent/assent form. We will stress that just because the adolescent participated in the baseline survey and/or the intervention activities they are not obliged to participate in the endline survey. We will also ask for consent/assent from adolescents participating in the coaching sessions and consent from their caregiver where necessary. Sports coaches will collect the signed consent/assent forms at the start of the sessions. For the process evaluation and community advisory groups, participants (adults and adolescents) interested in participating will be given a consent/assent form and information sheet. Participants (and caregivers) will be able to ask researchers any questions about the study either in person or by phone (contact details on the information sheet). Those who return signed consent/assent forms will be able to participate.

### Harms

There is no data safety monitoring committee for this trial: adverse events and severe adverse events will be reported to an independent trial steering committee. Participant information sheets will outline the research topic (mental health promotion) and, where applicable, participants will be asked about mental health problems. Researchers will be trained to ask questions in a sensitive and culturally respectful way and to conduct interviews/focus group discussions in a private space where participants feel comfortable. Participants will be reminded that they can stop or pause if they are uncomfortable and that they do not have to answer questions if for any reason they do not want to. If participants do become visibly distressed, researchers will ask if they would like to take a break or finish and will follow up with them individually. If participants disclose suicidal behaviour, the researcher will activate a standard operating procedure which involves arranging an urgent assessment by the TPO Nepal psychosocial counsellor who is based in the study area. Cases will be documented and submitted to the project coordinator and principal investigators for review.

Adolescents may disclose mental health problems and abuse to a coach or assistant coach during the intervention. The psychosocial counsellor will assess these cases and formulate a plan which may involve local health services and services for survivors’ support.

If adolescents incur an injury due to the intervention (e.g. during the sports coaching), coaches and/or assistant coaches will assess the severity, consult with the adolescent and their caregiver and help them to access appropriate health facilities if necessary. Coaches will have access to a basic first aid kit.

## Planned analyses

### Qualitative data

Audio recordings of qualitative interviews and focus group discussions will be transcribed in Nepali or Tharu and translated into English. We will analyse English transcripts along with observation notes using the Framework Method [38]. We will develop an analytical framework informed by the intervention theory of change and including deductive codes related to feasibility and acceptability. Several members of the research team will be involved in coding transcripts. All coders will initially code the same three transcripts and compare coding to check consistency.

We will take notes during meetings with community advisory groups which will inform the ongoing intervention process and process evaluation tools.

### Cost analysis

We will calculate the costs of setting up and implementing the intervention, compared with the control, from the provider perspective. Costs from monthly project accounts will be entered into an Excel costing tool, categorised as start-up or implementation costs and allocated to different cost centres (capital, staff and materials) and activities such as sports coaching or monitoring and evaluation. Costs related to research activities will be captured but excluded from the results. Project staff timesheets will inform how much of staff salaries should be allocated to set-up and implementation and across different activities. Staff will be asked about their time allocations at the end of manual development, ahead of implementation and at the end of implementation. Both financial and economic costs will be calculated. Indirect costs that are not captured by project accounts such as the opportunity cost of volunteer time or donated goods will be identified through project records and discussions with staff members and then assigned a value using local secondary data or assumptions. Results will include the total annual cost of SMART compared with the control, annual implementation costs, unit cost per adolescent and cost per cluster. One and two-way sensitivity analyses will be carried out by varying key inputs with uncertainty such as joint costs and staff time allocations.

### Mixed methods framework

Overall, we will use a fully mixed concurrent equal status mixed methods design that mixes qualitative and quantitative research across the research objectives, type of data and data inference [41]. In the process evaluation, quantitative findings relating to reach and fidelity will be explored through qualitative research, using a fully mixed sequential equal status design. We will use the Good Reporting of A Mixed Methods Study (GRAMMS) Framework to inform and describe the collection, analysis, integration and interpretation of quantitative and qualitative data [42].

## Progression criteria

Related to the study objectives, we have identified criteria to inform the decision to progress to a fully powered cRCT:Fidelity to the intervention manual—at least 75% of activities in each session completed at a satisfactory/superior level according to a fidelity checklist developed for the intervention.Exposure to the intervention—at least 30% of adolescents aged 12–19 living in the intervention clusters participate in at least five coaching sessions, measured in the endline survey. This is based on our assumption that 30% of adolescents need to participate to see effects at the community level and five sessions are sufficient for adolescents to build their psychosocial skills.Fewer than 10% of adolescents experience an adverse event (i.e. an untoward physical or psychological occurrence which is potentially related to the intervention) or a severe adverse event (i.e. an adverse event that is life-threatening, results in death and/or requires hospitalisation).Fewer than 15% missing items on mental health and wellbeing outcome measures at endlineFewer than 10% of adolescents living in the control clusters participated in the intervention.

Where criteria are not met, we will revisit the intervention/trial procedure in depth before progressing to a full trial.

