## Study design and methods

### Setting

Transcultural Psychosocial Organization (TPO) Nepal (www.tponepal.org) is leading the study with King’s College London (KCL). The study is in Bardiya district, in Lumbini Province, on the Indian border. In 2021, the estimated district population was 459,900 [19]. More than 50% are of Tharu ethnicity, indigenous to this area of Nepal, and more than half speak Tharu as their first language [20]. Eighty-three percent of men and 72% of women aged five and over can read and write [19]. The district has one hospital, three primary health centres and 30 health posts [21]. The most common sport in Bardiya is football but cricket, volleyball and *kabbadi* (a contact team sport popular across South Asia) are also played. Adolescents mostly engage in sport through school. Community football clubs exist but are mainly for boys. There are few opportunities for girls to play sport in the community.

Bardiya is administratively divided into eight municipalities. Each municipality is comprised of multiple wards. The study area is four communities of approximately 1000 population, the size of a small ward, in one of these municipalities. Each community represents one cluster. Communities will be selected on the basis that they are far enough apart and/or separated by natural boundaries (e.g. jungle or farmland) so that it is unlikely adolescents from the control communities will participate in activities in intervention communities; they are accessible to the study team by road; and they are ethnically diverse (and hence findings will be more generalisable to other areas of Nepal).

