**Fig. 1 Fig1:**
[figure not shown]
Overview of the SMART intervention

Adolescents can participate in one or more sports at the same time, attending as many or as few coaching sessions as they wish. Coaching for each sport will be implemented in parallel over 10 months. Coaching sessions will be 90 min and held twice per week on school premises or community sports grounds. Each session will include training on sports and psychosocial skills including interpersonal communication, self-awareness, assertiveness, coping and problem-solving. Adolescents will work on these skills through drills, games, role-play, discussions and relaxation exercises. They will be encouraged to apply the skills outside coaching sessions, in school and at home.

For each sport, sessions will be led by a locally recruited sports coach and an assistant coach. Coaches will be recruited through open advertisement and personal networks. Eligibility criteria include experience coaching in martial arts, dance or football and the ability to live in the study area for the duration of the intervention. Coaches will receive an 11-day training programme led by psychosocial counsellors covering concepts of adolescent mental health, orientation to SMART and the role of a SMART coach, foundational helping skills (empathy, verbal and non-verbal communication, listening, etc.), group facilitation skills, safeguarding, self-care and basic first aid. Coaches will practice sessions with small groups of adolescents and receive feedback from counsellors.

Through our formative research, we learned about some of the barriers to adolescents playing sport, especially among girls. These include girls feeling uncomfortable playing with boys and a male coach, feeling vulnerable and at risk of sexual assault and lack of knowledge about the rules of the sport. We will try to address these barriers in the intervention by (i) recruiting a female coach or assistant coach for each sport, (ii) running some sessions on school sports grounds where girls feel safe and do not have to travel far from their homes and (iii) assuming no previous knowledge or experience of the rules and providing an orientation in coaching sessions.

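### The severe-event definition leaves out a risk the protocol names, and the pooled 10% safety criterion cannot be failed by any single grave event

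*Protocol article*

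**What the plan says.** The safety item under Progression criteria reads "Fewer than 10% of adolescents experience an adverse event" and continues to include severe adverse events in the same count. An adverse event is "an untoward physical or psychological occurrence which is potentially related to the intervention". A severe one is "an adverse event that is life-threatening, results in death and/or requires hospitalisation". There is no separate limit for severe events and no trigger for a single event. If a criterion is missed, the intervention or trial procedure is to be re-examined in depth before a full trial.

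The SMART intervention section lists, among the barriers that girls described in the formative research, "feeling vulnerable and at risk of sexual assault". It gives responses: a female coach or assistant coach for each sport, some sessions on school grounds, and safeguarding as part of coach training.

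The Harms section expects disclosures: "Adolescents may disclose mental health problems and abuse to a coach or assistant coach during the intervention". It then says: "The psychosocial counsellor will assess these cases and formulate a plan which may involve local health services and services for survivors’ support". On oversight, it says that "adverse events and severe adverse events will be reported to an independent trial steering committee".

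**The concern.** SMART brings minors and coaches together twice a week for 10 months. The protocol records that girls feel at risk of sexual assault around sport, yet the severity grading has no category for assault or abuse, nor for lasting disability. Such an event, if it neither threatens life nor needs admission, is graded with minor sports injuries.

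The progression rule adds a second problem. Because it counts the share of adolescents with an event of either grade, it responds to how many are affected and not to how serious the event is. The pilot could report no severe harms and a safety criterion met after an assault connected with coaching. It could also report the criterion met after a death. Testing the safety procedures is one of the pilot's stated objectives, so a criterion that does not respond to grave events weakens what the pilot can say on that objective.

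**Working it through.** **1. The plan's own figures (Sample size section).** Ages 12–14: 10.4% × 3/5 = 6.24%. Ages 12–19: 11.2% + 6.24% = 17.44%, given as 17.4%. Four clusters of about 1000: 4 × 1000 × 0.174 = 696, which matches. With 20% living away: 696 × 0.8 = 556.8, given as 556, which matches.

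The same section gives 166 adolescents per cluster. That does not match 17.4% of 1000, which is 174, and 4 × 166 = 664, not 696. I use 696 because 556 follows from it.

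**2. How many affected adolescents the criterion allows.** The largest whole number strictly below 10% of n is ceil(0.10 × n) − 1. The criterion gives no denominator, so each n below is an assumption.

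| Assumed denominator | n | Largest count that passes | Share | Next count |
|---|---|---|---|---|
| All surveyed | 556 | 55 | 9.9% | 56 (10.1%) |
| All residents, intervention clusters (696/2) | 348 | 34 | 9.8% | 35 (10.1%) |
| Intervention clusters, 20% away (556/2) | 278 | 27 | 9.7% | 28 (10.1%) |
| 30% of 278 participating (83.4, rounded up) | 84 | 8 | 9.5% | 9 (10.7%) |

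With 166 per cluster, the intervention clusters would hold 332 residents and the limit would be 33 (9.9%), so the discrepancy in step 1 does not alter the conclusion.

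**3. Weight of one event.** One affected adolescent is 1/556 = 0.2%, 1/278 = 0.4% or 1/84 = 1.2%. Under every assumption, one event of any gravity leaves the criterion met by a wide margin.

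**4. Effect of changing the grading alone.** By the protocol's wording a severe adverse event is a kind of adverse event. The number of adolescents with either grade is therefore the same whether an assault is called severe or not. Moving it changes the severe count from 0 to 1 and leaves the criterion's numerator, denominator and limit as they were: 27 of 278 before, 27 of 278 after. The definition and the pooled limit are thus two separate faults, and each needs its own change.

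**5. The definition set against a named risk.** A sexual assault on the way to a session, without threat to life or need for admission, meets the adverse event definition, since it is untoward and potentially related. It meets none of the three severity conditions. The same holds for an injury that leaves a disability but needs no admission.

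**The case against.** The best defence is that the 10% limit governs progression only. It does not decide how a case is handled. Both grades go to the independent steering committee, disclosed abuse goes to the psychosocial counsellor, and disclosed suicidal behaviour has its own urgent procedure. The article also names safety standard operating procedures that are not shown, and its Discussion says that problems with safety procedures will be modified in the full trial protocol. All of this stands, and it rules out several stronger readings that a reader might infer:

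- **That the narrow definition is why an assault fits within the 10%.** It is not. Severe events sit under the same limit.
- **That an assault linked to coaching would not reach the steering committee.** Recorded as an adverse event, it would. The gap is smaller: Harms does not say that disclosed abuse linked to SMART is recorded as one. The disclosures expected there are not said to arise from coaching, and unrelated abuse is not an adverse event by the stated definition.
- **That there is no route for a complaint about a coach.** This is the kind of detail that a condensed article leaves to operating procedures. The advisory groups are also asked about unexpected harms.
- **That hospitalisation is a poor marker because "The district has one hospital, three primary health centres and 30 health posts" and one cluster pair is hard to reach.** The definition turns on whether admission is required, not on whether it was obtained.
- **That any suicide attempt without admission is non-severe.** Many would count as life-threatening.
- **That sexual assault is an observed hazard of SMART.** The formative finding is a feeling of risk reported as a barrier, and the protocol lists steps to address it.

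None of these answers the two points that remain. The definition and the limit are printed in the article, so they are stated rules and not details left elsewhere.

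**Conclusion.** The concern holds in two parts. The severe-event definition grades as non-severe an assault, or a disabling injury, that is neither life-threatening nor needs admission, although fear of sexual assault is recorded in the protocol itself. Independently, the safety criterion pools both grades, so no single grave event can fail it. It is met with up to 27 of 278 adolescents affected if the denominator is the intervention clusters with 20% away, and with 8 of 84 to 55 of 556 across the other assumptions. These counts rest on the expected numbers in the Sample size section and on a denominator that the protocol does not state. The finding concerns severity reporting and the progression decision. It does not show that cases would go unmanaged or unreported.

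**What to change.** **Progression criteria, definition.** Extend the severe category to assault or abuse connected with SMART staff, sessions or travel to them, and to events causing persistent disability, whether or not the adolescent is admitted.

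**Progression criteria, limit.** Take severe events out of the pooled 10% limit. State that any one potentially related severe event prompts steering committee review and the in-depth revisit before progression. Name the denominator for the limit that remains on other adverse events.

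**Harms.** State that disclosed abuse linked to SMART is recorded as such an event. Committee reporting needs no other change, because both grades already go there.

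**Cost.** Wording, and notice to the ethics committees and the steering committee, which the Trial status section already provides for amendments. A few more events will be labelled severe, and the criterion becomes harder to meet. A triggered review does not by itself prevent a full trial. It requires the event to be considered first.

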## Dissemination

We will publish findings from the trial in academic journals. We will organise dissemination events in Bardiya and Kathmandu, with national and local government officials, adolescents, caregivers, teachers, researchers and non-governmental organisations.

## Timeline

Recruitment and data collection for the baseline survey and facilitator training started in Jan 2023. Table 3 presents the SPIRIT (Standard Protocol Items: Recommendations for Interventional Trials) enrolment, interventions and assessment schedule.

**Table 3 Tab3:** SPIRIT schedule of enrolment, interventions, and assessments for SMART

	**Enrolment**	**Allocation**	**Baseline**	**Intervention implementation**	**Endline**
**Timepoint**	***-t***_***1***_		**t**_**0**_		***t***_***1***_
**Enrolment:**					
Identification of study clusters	X				
Cluster randomisation and allocation		X			
Adolescent eligibility screen			X		
Participant informed consent			X		
**Intervention:**					
*SMART*				X	
*Control*				X	
**Assessments:**					
*Warwick Edinburgh Mental Wellbeing Scale*			X		X
*Schwarzer Self-Efficacy Scale*			X		X
*Rosenberg Self-Esteem Scale*			X		X
*Adolescent Emotion Regulation Strategies Questionnaire*			X		X
*Multidimensional Scale of Perceived Social Support*			X		X
*Patient Health Questionnaire 9-item—modified for adolescents*			X		X
*Generalised Anxiety Disorder 7-item*			X		X
*Functional impairment tool*			X		X

## Discussion

We have developed a community sports intervention for adolescents in Nepal, which will help to address the scarcity of evidence-based mental health promotion interventions for children and adolescents in LMICs. Strengths of our study design include (i) an intervention informed by evidence at the local and global level working with locally available resources and personnel; (ii) a relatively long intervention period to maximise any benefits; (iii) a pragmatic cross-sectional evaluation approach to account for the mobility of adolescents, and to explore any effects of sport for those not directly participating in the intervention activities; and (iv) community advisory groups and a process evaluation to provide insight into how the intervention is being implemented and may effect change. Limitations of the study include the lack of blinding among coaches, assistant coaches, teachers and intervention supervisors, and the small number of clusters and potential baseline differences between control and intervention arms. Findings from the study will inform the decision to progress to a fully powered cluster-randomised controlled trial. Where findings point to feasibility and acceptability issues, for example in terms of randomisation, fidelity to the intervention manual, and safety procedures, these will be addressed and modified in the full trial protocol.

### Trial status

The trial is open and recruiting participants for the baseline survey. Any amendments to this protocol will be communicated to the Research Ethics Committees and trial steering committee.

## Data Availability

Data sharing is not applicable to this article as no datasets were generated or analysed during the current study.
